### Interventions

#### Nutritional Intervention

The nutritional intervention will be conducted by an experienced nutritionist. All participants receive nutritional guidance 30 days before the combined therapy and HIIT. This initial intervention aims to adjust macronutrient intake, optimize energy consumption, and improve diet quality by reducing the consumption of ultraprocessed foods and increasing the consumption of minimally processed foods. Macronutrient adjustments follow the recommendations of the dietary reference intakes, with carbohydrates comprising 45% to 65%, proteins comprising 10% to 35%, and lipids comprising 20% to 30% of the total caloric intake [60].

Following this phase, participants undergo a new series of assessments and then begin 5 weeks of combined therapy and HIIT. During these 5 weeks, dietary control is monitored by the nutritionist to ensure consistency in dietary patterns throughout the study. Daily energy intake is considered stable if variations remain at <10% during the protocol.

Food intake will be assessed weekly using a 24-hour recall, a questionnaire that quantifies all food and drink consumed in the previous 24 hours. Participants will receive an electronic link once a week during the 5-week intervention. The data collected will be analyzed by a nutritionist to assess consistency and adherence in total energy and macronutrient intake. Variations of >10% in total calorie intake will be discouraged to ensure dietary stability throughout the protocol. No additional methods of validating adherence to the diet will be used as the weekly recalls provide a feasible and easy monitoring strategy for the participants. Total energy intake and macronutrient composition will be calculated using the Dietbox program [61]. Energy requirements will be estimated based on the dietary reference intakes [62]. For qualitative analysis, foods will be categorized according to their processing level—natural, minimally processed, culinary ingredients, processed, and ultraprocessed—as defined by the 2014 Food Guide for the Brazilian Population [63].

#### Combined Therapy Application Time Calculation

Before the first session, the application time for the combined therapy will be individually determined. Measurements will be conducted by the same blinded assessor using an inelastic tape measure with the participant in a standing position. Specifically, the horizontal distance between the last floating ribs (x) and the vertical distance to the midpoint between the anteroinferior iliac crests (y) will be measured. The abdominal area (cm^2^) will be calculated by multiplying these 2 values (x × y) and then dividing the result by 18. This divisor corresponds to the total effective radiating area of the ultrasound head used in the therapy, which consists of 3 spheres, each with an effective radiating area of 6 cm^2^. Dividing the abdominal area by 18 allows us to determine the time required to apply the therapy to each participant according to the following formula: application time = (x × y)/18.

For example, if a participant has a horizontal distance (x) of 21 cm and a vertical distance (y) of 26 cm, the area will be calculated as follows: 21 × 26 = 546 cm^2^. Dividing this area by 18 results in approximately 30 minutes of application time (546/18 = 30.33 minutes).

#### Pretraining Instructions

Before each training session, participants will be instructed to (1) wear comfortable clothing and exercise-appropriate footwear, (2) ensure adequate sleep the previous night, (3) hydrate with water 2 hours before the session and bring a personal water bottle, and (4) avoid strenuous physical activity and alcoholic consumption within 24 hours before the session.

Food consumption will also be recommended 24 hours before the first and last sessions, as described in the Nutritional Intervention section.

#### Session Scheduling and Follow-Up

To minimize data loss, participants receive reminders about the date and time of each session. Physiotherapists responsible for interventions may also call participants if necessary to confirm appointments. For evaluations and re-evaluations, the blinded evaluator contacts the participants via telephone. At the end of the 10 treatment sessions, the re-evaluation is scheduled between 3 and 15 days after the last session.

### Group 1: AG

Participants in the AG will be treated with TUS+Aussie current (Heccus; Ibramed). All therapists who will administer the TUS+Aussie current interventions have undergone standardized previous training, which includes theoretical and practical sessions to ensure the fidelity of the protocol. In addition, every participant will be seen by each therapist at least once. This strategy aims to minimize possible biases related to therapist application and intervention quality in all groups.

The protocol combines continuous ultrasound (3 MHz; 2 W/cm^2^) and Aussie current (1 kHz; modulated at 10 Hz). The participant will be instructed that the sensation must be tingling and comfortable (sufficient intensity to produce strong but comfortable paresthesia without stimulation to painful paresthesia) [64]. In every session, and every 5 minutes, the therapist will record the intensity of the Aussie current and evaluate the levels of paresthesia on a scale from 0 to 10, with 0=no tingling sensation and 10=maximum tolerable tingling. Given the possible habituation to the paresthesia caused by the Aussie current, the scale will be applied every 5 minutes during the session, and a score of 5 will be set as the threshold for adjusting the intensity of the current (ie, tolerable or supportable tingling). The target intensity is set at approximately 5. The intensity of the Aussie current will be adjusted immediately whenever the perception reported by the participant falls to <5 (0-10), ensuring a consistent and comfortable sensory experience throughout the session.

The treatment is applied to the abdominal region using ultrasound. The therapist ensures consistent pressure and maintains slow, slightly circular, horizontal movements without losing contact with the surface.

In the final session, participants complete a printed questionnaire that includes the reported intensity of the Aussie current and the following questions: “Would you recommend this therapy to someone else?” and “Do you believe you received the active treatment, the placebo or are unsure? Why?” In addition, in the last session, the blinded therapist will answer a questionnaire about which group they believe each participant was allocated to and the reason for this choice.

Immediately after the TUS+Aussie current application, participants will take to the treadmill for the HIIT session. Participants will be instructed to maintain proper posture with relaxed shoulders, a forward-facing stance, and a breathing pattern of inhaling through the nose and exhaling through the mouth, avoiding apnea during the exercise. The Borg scale (6-20) [65] will be applied 10 seconds before each load change during the 20-minute interval protocol.

HR is continuously monitored using a Polar H10 HR monitor attached to an elastic chest strap positioned at the xiphoid process. This Polar monitor is paired via Bluetooth with a tablet.

The HIIT protocol lasts 30 minutes and includes the following:

A warm-up of 5 minutes, progressively reaching 55% to 60% of the peak HR determined in the ergometric test.An interval phase of 10 cycles of a 1-minute high-intensity interval (85%-90% of peak HR) interspersed with 10 cycles of a 1-minute light- to moderate-intensity interval (55%-60% of peak HR). After 5 sessions, the load will be updated by 5% to 10% considering physiological adaptations (moderate intensity 60%-65% of peak HRand high intensity 90%-95% of peak HR). After the fifth training session, the training load will be adjusted by 5% to 10% based on physiological (peak HR) and subjective (Borg) criteria. Specifically, participants who consistently reach the target HR zone (85%-90% of peak HR) during high-intensity intervals and report a perceived exertion score of <17 on the Borg scale (6-20) will have the speed or incline of the treadmill increased by 5% to 10%. HR will be monitored continuously using an HR sensor, and the Borg rating of perceived exertion will be applied 10 seconds before each load change.A cooldown and recovery phase of 5 minutes of active cooldown followed by passive recovery with the participant seated (Figure 1).Guidelines and organization will include controlled temperature and humidity (21-24 °C and 40%-60%, respectively) and previous hydration with water.

**Figure 1 figure1:**
[figure not shown]
Summary of the high-intensity interval training (HIIT) protocol following the application of combined therapy, along with the progression of the intervention protocol. HRpeak: peak heart rate during the ergometric test; TUS: therapeutic ultrasound.

### Group 2: PG

All the participants in this group will follow the same procedures and sequence as those in the AG. However, the PG participants will receive the TUS and Aussie current treatment in placebo form, ie the therapy switched off. The protocol combines continuous ultrasound (0 MHz; 0 W/cm^2^) and Aussie current (0 kHz; modulated at 0 Hz). Immediately after the TUS+Aussie current treatment, all participants proceed to the treadmill to start the HIIT, following the same protocol as for the AG (Figure 2).

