## Methods

### Study Design

This is a randomized, pragmatic, placebo-controlled, double-blinded, 3-arm (1:1:1) clinical trial. The protocol was developed in accordance with the SPIRIT (Standard Protocol Items: Recommendations for Interventional Trials) guidelines [23].

This research will be conducted at the Federal University of São Carlos (UFSCar) in the Cardiovascular Physical Therapy Laboratory/Physical Exercise Research Center within the Department of Physical Therapy. Participants will be recruited through social media advertisements. An electronic form hosted on Google Forms will be shared via Instagram. Interested participants who meet the basic inclusion criteria will be contacted via WhatsApp to provide additional information about the study and assess their eligibility. Participants who do not respond to the messages will receive up to 3 phone call attempts at different times. If these contact attempts are unsuccessful, the individual will be considered unreachable and ineligible for the study.

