### Randomization and Blinding

In this study, the researchers responsible for the evaluations and those analyzing the data will be blinded. To ensure the feasibility of blinding, the blinded research teams will not participate in the interventions, and all information will be coded to prevent the identification of participants and intervention groups. The effectiveness of blinding will be assessed using a questionnaire completed by the evaluators at the end of the final assessment for each data collection block.

After the initial assessments, participants will be stratified (age range, sex, and fat mass index) and randomly assigned to 1 of 3 groups. Participants in group 1 (active TUS+Aussie current with HIIT [AG]) will undergo combined therapy (TUS+Aussie current) along with the HIIT protocol. Participants in group 2 (placebo for TUS+Aussie current with HIIT [PG]) will undergo placebo combined therapy (TUS+Aussie current) with the devices turned off along with the HIIT protocol. Participants in group 3 (TUS+Aussie current–only group [HG]) will receive only the combined therapy (TUS+Aussie current) without the HIIT protocol.

For stratified randomization, participants will be initially grouped into blocks based on similar characteristics, including age range (20-29 years or 30-40 years), sex (male or female), and fat mass index (overweight, grade-I obesity, or grade-II obesity). These characteristics will be chosen to control for potential confounding factors. Within each block, participants will be then randomized into the 3 study groups using Microsoft Excel, ensuring an unbiased allocation process. Block sizes were not fixed, further reducing the risk of allocation predictability. The randomization process will be conducted by a researcher designated exclusively for this task, who will have no contact with the study participants or the researchers involved in data collection. This researcher will also be responsible for generating random alphanumeric codes to ensure the anonymity of each participant’s information.

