### Strengths and Weaknesses of This Study

This is a randomized, double-blind, placebo-controlled study designed in accordance with the most rigorous standards for conducting and processing data in clinical trials, ensuring the reliability of the results. It is important to highlight that the intervention period was defined to assess whether the intervention protocol, considering the usual recommendations for exercise and diet, as well as the number of TUS+Aussie current application sessions commonly offered by aesthetic clinics, results in fat reduction for patients with obesity. Thus, this study will provide health care and aesthetic professionals with scientific evidence to understand the mechanisms involved in applying the studied therapies, expected results, and potential systemic impacts. To achieve these objectives, this study includes several outcome measures, including SAT thickness, body composition, metabolic profile, and serum glycerol release, allowing for a comprehensive evaluation of the combined effects of TUS+Aussie current and HIIT. In addition, by incorporating secondary outcomes such as CAM, sleep quality, and perceived stress, this study offers a broader understanding of the physiological and psychological effects of the intervention.

Despite these strengths, this study presents some limitations. The sample size, though adequate for preliminary findings, may not be large enough to detect differences in CAM results. In addition, individual variations in adherence to the HIIT protocol and lifestyle factors such as diet and physical activity outside the study can influence the results. However, it is important to note that strict guidelines are provided to minimize these influences, ensuring greater control over external variables and the reliability of the findings. Furthermore, the study population consists of individuals with overweight and obesity, which may limit the generalizability of the findings to other populations, such as those with severe obesity or metabolic disorders.

In summary, this study will provide a robust framework for evaluating the combined effects of TUS+Aussie current and HIIT on body composition, CAM, and cardiorespiratory and metabolic health. Despite this study’s limitations, the findings will contribute valuable insights into noninvasive strategies for obesity management and may support future research and clinical applications.

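### The switched-off placebo cannot be run under the tingling-based procedure assigned to it, so treating therapists are not blinded, participant masking is doubtful, and the unqualified double-blind label is too broad

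*Protocol article*

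**What the plan says.** On the placebo, the section Group 2: PG states: "All the participants in this group will follow the same procedures and sequence as those in the AG". It then gives the difference, namely treatment "in placebo form, ie the therapy switched off", with settings as follows: "The protocol combines continuous ultrasound (0 MHz; 0 W/cm^2^) and Aussie current (0 kHz; modulated at 0 Hz").

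The procedure that PG inherits is in Group 1: AG. Participants are told to expect a comfortable tingling. In every session, at 5-minute intervals, the therapist records the current intensity and takes a paresthesia rating in which 0 means no tingling. The target is about 5, and "The intensity of the Aussie current will be adjusted immediately whenever the perception reported by the participant falls to <5 (0-10"). Monitoring Adverse Events repeats the target of about 5 without restricting it to the arms that receive current.

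On blinding, the protocol speaks in several ways:
- The abstract attaches a definition to double-blind: researcher and outcome assessor.
- Randomization and Blinding names evaluators and data analysts, and adds that "the blinded research teams will not participate in the interventions".
- Study Design carries no such limit: "This is a randomized, pragmatic, placebo-controlled, double-blinded, 3-arm (1:1:1) clinical trial".
- Strengths and Weaknesses of This Study also has none: "This is a randomized, double-blind, placebo-controlled study designed in accordance with the most rigorous standards".
- Group 1: AG says that in the last session "the blinded therapist will answer a questionnaire about which group they believe each participant was allocated to". It also asks participants whether they think they had active treatment or placebo, or are unsure.

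**The concern.** A placebo equalises expectation only if the people receiving it cannot tell. Here the procedure repeatedly draws attention to a sensation that a switched-off device does not produce, and the person operating the device can see that it is off.

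AG versus PG is the only contrast that isolates the device. AG versus HG (the group with TUS and current only) and PG versus HG both differ by HIIT, which no sham can hide. If PG participants recognise the placebo, the AG-PG difference in a self-reported score mixes a device effect with expectation. Three of the six secondary rows in Table 2 are self-reported: sleep quality; anxiety, depression and stress; and body image.

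A further problem is that a guess about allocation from someone who operates the device carries no information about whether blinding worked.

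**Working it through.** The point is one of consistency and depends on no sample size or power figure, so the passages are set side by side.

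**Step 1. Can the AG procedure be carried out in PG?** Group 2: PG sets every output to zero. On the scale in Group 1: AG, an accurate rating with no current is 0. Since 0 < 5, the adjustment rule is triggered at every check, and no adjustment can satisfy it while the device stays off. Group 2: PG describes no altered script, sham sensation or masked console. As written, the two sections cannot both be followed.

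**Step 2. How often does the conflict arise?** The example under Combined Therapy Application Time Calculation gives about 30 minutes per application. Ratings per session: 30 / 5 = 6. Over the 10 planned sessions: 6 × 10 = 60. This count is for that one example; application time is individual.

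**Step 3. Who learns the allocation?**
- *Treating therapists.* They record the current intensity at each check, and in PG there is none. Group 1: AG also has every therapist see each participant at least once, so no therapist is kept away from the PG sessions. They know AG from PG.
- *Participants in PG.* They are told to expect tingling and feel none, which is a strong cue repeated at each check. That they infer the arm is likely but not certain.
- *Evaluators and analysts.* They take no part in the sessions and data are coded. Nothing in Steps 1 and 2 unblinds them directly. A participant who knows the arm could disclose it, and Initial Evaluation puts all assessments in the hands of one team member, but the documents do not show that this happens.

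**Step 4. Do the blinding statements agree?** If the therapist called blinded in Group 1: AG is the treating therapist, the statement conflicts with Step 3 and with the rule in Randomization and Blinding that keeps blinded teams out of the interventions. The labels in Study Design and in Strengths and Weaknesses omit the limit that the abstract states.

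**Step 5. Illustration only.** The documents give no size for an expectation effect. Assume spurious shifts of 0.2 and 0.3 SD in a self-reported score, 18 per arm (the number in Sample Size before dropout), and an unadjusted two-sided two-sample t test at 5% with 34 degrees of freedom.
- Noncentrality = shift × √(18/2) = shift × 3, that is 0.6 and 0.9.
- Chance of declaring an AG-PG difference with no true device effect: about 9% and 14%, against 5% with no shift.
- With a Sidak level for three pairs, 1 − 0.95^(1/3) = 0.017, the same shifts give about 4% and 6%, against 1.7%.

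The planned analysis is a mixed model with Sidak comparisons after a significant F, so neither set of figures is the error rate of the plan.

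**The case against.** The strongest reply is that double-blind is a defined term here. The abstract confines it to researcher and outcome assessor, and Randomization and Blinding to evaluators and analysts. No sentence says that participants are blinded, and a sham without sensation does not unblind evaluators or analysts. This stands. A reader might infer that the double-blind, placebo-controlled property fails outright; the documents do not support that. Blinding as the abstract defines it is not shown to fail, and a placebo arm does exist. What is in doubt is its credibility.

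A reader might also infer that participants cannot be blinded at all. That is too strong. Anyone treated with electrophysical agents for body mass in the previous 12 months is excluded, so many participants will have no recent comparison, and the final-session question measures what they believe.

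The blinded therapist may mean the assessing physiotherapist. That reading is possible, but the same section uses the word therapist for the device operator, so the text needs clarifying either way.

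It can be said that the sentence setting output to zero is an evident exception to the shared procedure, with detail left to the full protocol. This stands in part. The article could leave out the PG script, but it positively states that the AG procedures apply, and the safety section repeats the tingling target with no exception.

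Finally, the primary outcomes are ultrasound, DXA and serum measures. HIIT is steered by heart-rate zones and diet is followed weekly by a nutritionist. That stands: a route to the primary outcomes through effort (Borg ratings inform progression) or diet is possible but speculative.

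**Conclusion.** The point holds in limited form. It is certain from the text that the rating-and-adjustment rule cannot be met with the device off, and that treating therapists know AG from PG. It is likely, not certain, that PG participants infer their arm; this assumes that they report honestly and that no undescribed sham feature exists. It follows that the therapist described as blinded cannot be the treating one, and that the label in Study Design and in Strengths and Weaknesses claims more than the abstract and the blinding section support.

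The consequence falls on AG versus PG in three of the six secondary rows of Table 2. Its size cannot be derived from the documents. The percentages in the working rest on assumed shifts and a simplified test, and the conclusion does not depend on them.

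**What to change.** 1. In Study Design and in Strengths and Weaknesses, limit the label to outcome-assessor and analyst blinding. State that treating therapists are not blinded and that participant masking is not assured.
2. Reconcile Group 1: AG and Monitoring Adverse Events with Group 2: PG, stating how the tingling rating and the adjustment rule apply when the device is off. Leave the active-arm procedure as it is: recruitment began in February 2024, and a new script for all arms would treat earlier and later participants differently and could alter how the active current is set.
3. Remove the reference to a blinded therapist, or state that it means the assessor. Use the evaluators' questionnaire already planned in Randomization and Blinding as the test of blinding, and report participants' guesses by arm.
4. State that AG-PG differences in sleep, anxiety, depression, stress and body image are interpreted as not reliably participant-blinded.

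These are changes of wording and reporting that can be made before analysis, with no new staff or measurements. The cost is a less favourable blinding claim.
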